Data will be analyzed at the level of clinics, clinicians, and patients and stratified by the study phase. Bi-variate analyses will be used to assess differences in outcomes between the intervention and control periods. We will also follow the CONSORT 2010 [30] extension to stepped-wedge trials when reporting results. The percentages of FH diagnostic evaluations completed will be reported every six months. Follow-up will continue through the end of the study (48-months). Characteristics of clinicians and clinics will be summarized by exposure status to allow consideration of selection bias and lack of balance. FH diagnostic evaluation rate will be analyzed using a generalized linear mixed effects model [31,32], with completion of the FH diagnostic evaluation as a binary outcome, intervention, time, and their interaction as fixed-effects, cluster as random-effects, along with other covariates as predictors. The covariates will be selected by the advisory board based on previous evidence of the effect on FH diagnostic evaluation rates. A mixed effects model will be used to account for the hierarchical clustering structure of data (patients per clinician, clinicians per clinic). The model assumes that the intervention effect and time effects are common to all clusters, and that observations are equally correlated within clusters across time. In the primary analysis, adult and pediatric clinics will be analyzed separately however commonalities will be sought and, when appropriate, pediatric, and adult behavior will be compared. Of particular interest are differences in performance among adult and pediatric clinicians. Sample sizes were based on a power calculation considering a meaningful implementation strategy package as a 20% improvement in FH diagnostic evaluation rate and required a minimum of 10 clinics per region. Statistical analyses will be conducted using RStudio (Version 1.3.1093) [33]. *p*-values of less than 0.05 are considered statistically significant.

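### The primary model fixes equal within-clinic correlation over 48 months; if that correlation falls with time, the standard error is too small and the 5% error rate is exceeded

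*Protocol article*

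**What the plan says.** The section on data collection and analysis for adoption and penetration, under Aim 2, sets out the primary analysis. It is a generalized linear mixed model "with completion of the FH diagnostic evaluation as a binary outcome", with "intervention, time, and their interaction as fixed-effects, cluster as random-effects, along with other covariates as predictors". The model is meant to "account for the hierarchical clustering structure of data (patients per clinician, clinicians per clinic"). Two assumptions are then stated. The first is "The model assumes that the intervention effect and time effects are common to all clusters". The second follows on directly: "and that observations are equally correlated within clusters across time". No clinic-by-period term or decaying correlation is named.

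The same section sets follow-up at 48 months with six-monthly reporting, and analyses adult and pediatric clinics separately. The opening of Aim 2 makes the clinic the unit whose order is randomized. It also provides for review and adjustment of the package following every step, and gives refresher sessions where trainees change as an example.

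**The concern.** Under the stated assumption, two patients seen at one clinic nearly four years apart are as alike as two seen in the same month. A stepped wedge takes much of its information from before/after contrasts within clinics. The more correlation a model credits between periods, the more clinic-level variation it believes cancels in those contrasts. If the true correlation weakens with time, less cancels than the model supposes, and its standard error is too small.

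At stake are the confidence interval and the p<0.05 test for the primary outcome. A second, smaller matter is wording. The random-effects sentence names only cluster, while another sentence in the same paragraph promises patients within clinicians within clinics. The contextual-inquiries part of section 3.1.1 lists cluster-level covariates apart from clinic-level ones, so the word is not used in one clear sense.

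**Working it through.** **The plan's own figure.** The article requires at least 10 clinics per region to detect a 20% improvement. This cannot be reproduced: baseline rate, power, ICC, CAC and patients per clinic-period are not given, nor whether 20% is absolute or relative. Only 10 × 4 regions = 40 clinics carries forward.

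**Inputs from the article.** At least 40 clinics, 4 steps, clinic as the randomized unit, significance level 0.05.

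**Assumed.** T = 5 periods (a baseline and one per step), 10 clinics crossing per step, equal cluster sizes, m = 5 to 50 patients per clinic-period, ICC 0.01 to 0.10, CAC 0.6 to 1.0. The binary model is approximated by a linear one with total variance 1 and one treatment effect. Cluster is taken as clinic.

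**Method.** Let the truth be nested-exchangeable: correlation ICC within a clinic-period, and ICC × CAC between periods of the same clinic. With J a matrix of ones and I the identity, the covariance of a clinic's period means is

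V = ICC·[CAC·J + (1−CAC)·I] + [(1−ICC)/m]·I.

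The stated model fits W = t·J + (s/m)·I. Under V its components settle at

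s = (1−ICC) + (T−1)·m·ICC·(1−CAC)/(Tm−1),

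t = ICC·CAC + ICC·(1−CAC)/T + (1−ICC)/(Tm) − s/(Tm).

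Model SE² is the treatment element of A⁻¹, with A = ΣX'W⁻¹X. True SE² is the treatment element of A⁻¹(ΣX'W⁻¹VW⁻¹X)A⁻¹. With r = model SE / true SE, type I error = 2[1 − Φ(1.96·r)]. With equal numbers per step, the number of clinics cancels from r.

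**Hand check on one before/after contrast** (ICC 0.05, CAC 0.8, m = 20):

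- s = 0.95 + 4×20×0.05×0.2/99 = 0.9581.
- True variance = 2[ICC(1−CAC) + (1−ICC)/m] = 2(0.0100 + 0.0475) = 0.1150.
- Model variance = 2s/m = 2×0.9581/20 = 0.0958.
- r = √(0.0958/0.1150) = 0.913.

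The full design gives 0.921, so 1.96 × 0.921 = 1.805 and type I error is 7.1%.

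**Full design, nested-exchangeable truth, 5 periods:**

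| ICC | CAC | m | r | true SE / model SE | type I error |
|---|---|---|---|---|---|
| any | 1.0 | any | 1.000 | 1.00 | 5.0% |
| 0.01 | 0.9 | 5 | 0.999 | 1.00 | 5.0% |
| 0.05 | 0.9 | 20 | 0.958 | 1.04 | 6.0% |
| 0.05 | 0.9 | 50 | 0.896 | 1.12 | 7.9% |
| 0.05 | 0.8 | 20 | 0.921 | 1.09 | 7.1% |
| 0.05 | 0.8 | 50 | 0.820 | 1.22 | 10.8% |
| 0.10 | 0.6 | 5 | 0.935 | 1.07 | 6.7% |
| 0.10 | 0.6 | 50 | 0.574 | 1.74 | 26.1% |

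**Other truths.** Suppose instead that correlation decays exponentially, with CAC the share retained per period. At ICC 0.05, CAC 0.8 and m = 20, r is 0.878 (8.5%) with 5 periods and 0.804 (11.5%) with 8 six-month periods. The last row of the table becomes 31.7% and 40.5%. Under the nested truth, going to 8 periods changes little (7.2% against 7.1%). Every case with CAC below 1 gave r below 1.

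**Clinician level.** Fitting only a clinic intercept when a clinician effect constant over time also exists (4 clinicians per clinic, 5 patients each per period) gives r = 1.017 to 1.040 and type I error of 4.1-4.6%. The error is then in the cautious direction.

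**The case against.** The strongest reply is that nothing in the article shows decay. It gives no ICC or CAC, and with CAC = 1 the model is exactly right. Refresher sessions could even hold a clinic's performance steady. This stands, and a reader who infers that the standard error is certainly too small goes further than the document allows. The follow-up length and expected changes make decay plausible; they do not prove it.

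A reader might also infer that equal correlation contradicts the clinician-within-clinic hierarchy. That is not supported. Nested clinic and clinician intercepts are themselves constant over time, so the assumption can be read as being about time lag alone, and both sentences can hold. What remains is that cluster is undefined. Nor does leaving out a stable clinician level shrink the standard error; the calculation shows the reverse. Clinician turnover would matter, but through decay.

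The sizes rest on chosen inputs and on a single effect, whereas the plan also includes an intervention-by-time interaction; inflation for that exact model was not computed. This limits the figures, not the direction found for a single effect.

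Finally, the analysis plan was still to be finalized (section 3.1.3), and a full version may hold sensitivity analyses. Their absence here is no defect. The equal-correlation assumption is different: the article states it for the primary model.

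**Conclusion.** The point holds conditionally. The article commits the primary model to correlation that is constant over 48 months, in a setting where it may well fall. If it falls, the model-based standard error is too small and the test exceeds 5%.

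The low end of the range is no inflation at all. At ICC 0.05, CAC 0.8-0.9 and 20-50 patients per clinic-period, the standard error is understated by a factor of 1.04 to 1.22 and type I error is about 6-11%. The 26% figure belongs to an extreme corner (ICC 0.10, CAC 0.6, 50 patients) and should not be read as the expected case. These figures assume a nested-exchangeable truth, equal cluster sizes, five periods and a linear approximation; exponential decay makes them larger. The undefined cluster is a separate point of clarity and adds nothing to the inflation.

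**What to change.** - Replace the equal-correlation assumption by adding a clinic-by-period random intercept, or a correlation that decays with time, to the primary model.
- Define cluster, and state clinic and clinician-within-clinic as the random-effect levels, so that the model sentence agrees with the stated hierarchy.
- Name a robust variance with a small-sample correction as the fallback if the extra variance components cannot be estimated. This matters because adult and pediatric clinics are analysed separately, and section 2.2 counts only 22 pediatric clinics.
- Restate the power calculation under the same structure, with its ICC, CAC and clinic-period size.

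The edits are a few lines of text and model code, plus the power rerun. The statistical cost is a wider interval and more variance components to estimate in a binary model. In the nested 5-period setting, fitting the correct structure raises the reported standard error by about 4% at ICC 0.05, CAC 0.9 and 20 patients, about 21% at CAC 0.8 and 50 patients, and about 70% in the extreme corner. If correlation really is constant, the added variance should be estimated near zero and little is lost. Whether 10 clinics per region still suffices cannot be judged from the article.

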### 2.2. FH Diagnostic Evaluation Program

This program for FH care is based on the current paradigm for notification regarding actionable genetic variants in MyCode Community Health Initiative (MyCode) a research program that links exome sequence data with electronic health record (EHR) data and returns pathogenic variants in clinically actionable genes to patient-participants (Figure 2) [13,20,21,22,23,24,25]. Evaluation is triggered by the notification of the patient and primary care clinician of an actionable variant. In CARE-FH, there will be four possible triggers: the presence of an FH variant from MyCode, cascade screening of family members identified in the MyCode program, identification of patients requiring an FH workup through applications of FH screening algorithms of EHR data, or presence of an LDL-C ≥ 160 mg/dL in a child. Notification will lead to scheduling a medical appointment to complete the FH diagnostic evaluation. Successful completion of the FH diagnostic evaluation, the primary outcome of this study, will include evidence the clinician has completed evidence-based FH diagnostic evaluation and management goals. The goals are defined as completing one of the following:-Used FH clinic note to document care-Added FH diagnosis on the problem list or used the Dutch Lipid Clinic Network score (DLCN) tool to exclude FH diagnosis-Used the FH smart-set (i.e., ordered a genetic test for FH)-Made a referral to the lipid clinic [12]-Initiate evidence-based lipid lowering medications

A patient will be considered to have FH if they have a positive genetic test for FH or have a DLCN > 8 and probable FH with a score of 5–8. Geisinger primary care sites are divided by geographic region (Central, Northeast, Western, or Geisinger Medical Center) and into several practice types. Adult-oriented primary care clinics are staffed by internists, family practitioners, and advanced practice professionals (physician assistants and nurse practitioners). Pediatric practices provide primary care and acute care at 22 clinics.

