## 4. Specific Aim 2 (R33): Compare FH Diagnostic Evaluation Rates among Primary Care Clinicians Who Receive the Implementation Strategy Package versus Those Who Do Not

We will conduct a type 3-hybrid effectiveness-implementation trial using a stepped-wedge design to test the effectiveness of the implementation strategy package designed in the R61 phase of the project [29]. The rollout will occur by Geisinger geographic region: Central, West, Northeast, and Geisinger Medical Center. Clinics within each region will be randomized as to the order of receiving the implementation intervention. Data will be collected on the primary and secondary outcomes before and after the intervention to measure change. After each step, we will use an iterative review process to re-assess the fit of the multi-level implementation strategy package and make adaptations, such as repeat sessions for clinics with new trainees, as needed. This aim will examine implementation outcomes including adoption and penetration of an FH diagnosis program (Table 2). We hypothesize: That clinicians that receive the implementation strategy package will have an improved rate of diagnostic evaluation for FH compared to those in the usual care group.

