### Data Collection and Analysis for Adoption and Penetration

All primary care clinics in the Geisinger system will be included in the study. Clinicians who have a patient who requires diagnostic evaluation for FH will receive an EHR-based notification. The clinician or designee will call the patient to discuss the next steps and schedule an appointment for an FH diagnostic evaluation (Figure 2). At the same time, adults, or parents of pediatric patients, will be notified by mail and telephone of the need for evaluation.

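### The sample size rests on at least 10 clinics per region, but the separate pediatric primary analysis has only 22 clinics across four regions, so the stated size does not support it

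*Protocol article*

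**What the plan says.** The sample size is given in one sentence of the section on data collection and analysis for adoption and penetration (Specific Aim 2). The power calculation assumed a "20% improvement in FH diagnostic evaluation rate and required a minimum of 10 clinics per region". The sentence does not say whether the clinics counted are adult, pediatric or both.

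Four other statements bear on it:

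- Analysis (same paragraph): "In the primary analysis, adult and pediatric clinics will be analyzed separately". The plan adds that adult and pediatric behavior will be compared when appropriate, and it singles out differences in performance between the two groups of clinicians as a special interest.
- Regions (Section 4): "The rollout will occur by Geisinger geographic region: Central, West, Northeast, and Geisinger Medical Center". That is four regions. The order in which clinics receive the intervention is randomized within region.
- Pediatric clinics (Section 2.2): "Pediatric practices provide primary care and acute care at 22 clinics".
- Eligibility (Specific Aim 2, data collection): "All primary care clinics in the Geisinger system will be included in the study".

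**The concern.** A sample-size statement should refer to the analysis that carries the primary conclusion. Here the primary analysis is two analyses, one per practice type, but there is one clinic minimum, and it is larger than the whole supply of pediatric clinics.

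What is at stake is how the pediatric result is read. Someone who sees a single power statement beside two primary analyses will apply it to both. A non-significant pediatric result could then be taken as adequately powered evidence that the implementation package does not work in pediatric practice, when the article gives no basis for that.

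**Working it through.** **The plan's own figure.** The minimum of 10 clinics per region cannot be reproduced. The article gives neither the target power, the baseline evaluation rate, the number of patients per clinic nor the intracluster correlation, and it does not say whether the 20% is absolute or relative. An article may leave such inputs to the full protocol, so their absence is not the point. The check below needs only a count.

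**The count.**

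- Minimum over all regions: 10 × 4 = 40 clinics.
- Pediatric clinics available: 22, which is 22/40 = 55% of that minimum and 40 − 22 = 18 short.
- Mean per region: 22/4 = 5.5.
- Regions that could reach 10 under any distribution: at most 2, since 3 × 10 = 30 exceeds 22.
- Clinics that could be added: none, because the whole system is already included.

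**The two readings of the minimum.**

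1. It applies to each separate analysis. The pediatric analysis then cannot meet it in at least two of the four regions.
2. It counts adult and pediatric clinics together. It may then be met, but it sizes a pooled analysis that the plan does not name as primary. For example, 22 pediatric and 18 adult clinics, suitably spread, would make 40 in total while neither separate analysis had 40. The pediatric analysis has no stated size basis.

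**What the shortfall might cost (illustration only).** Assume a two-sided 0.05 test, equal clinic sizes, and information proportional to the number of clinics. The standard error grows by √(40/22) = 1.35, and so does the detectable effect. With 22 clinics,

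power = Φ((1.960 + z) × √(22/40) − 1.960),

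where z is the normal quantile of the power assumed at 40 clinics and √(22/40) = 0.742.

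- From 80%: (1.960 + 0.842) × 0.742 − 1.960 = 0.12, power about 55%.
- From 85%: (1.960 + 1.036) × 0.742 − 1.960 = 0.26, power about 60%.
- From 90%: (1.960 + 1.282) × 0.742 − 1.960 = 0.44, power about 67%.

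The starting powers are assumptions. As a second illustration, the Hussey-Hughes stepped-wedge variance was used with four steps, five periods and an assumed intracluster correlation of 0.05. The 40 clinics were spread 10 per step and the 22 clinics 6, 6, 5 and 5. Rates and patient numbers are also assumed.

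| Evaluation rate, control to intervention | Patients per clinic-period | Power, 40 clinics | Power, 22 clinics |
|---|---|---|---|
| 40% to 60% (20 points absolute) | 2 | 77% | 51% |
| 40% to 48% (20% relative) | 20 | 85% | 61% |
| 40% to 60% (20 points absolute) | 10 | above 99% | 98% |

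The loss runs from negligible to large, depending on inputs that the article does not give.

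**The case against.** The strongest reply is that the sentence asks for 10 clinics per region, not 10 pediatric clinics. Regions contain both practice types, rollout is by region, and all clinics take part, so counting every clinic in a region is at least as natural. On that reading nothing shows that the minimum is missed, and power by practice type may be in the full protocol. This stands as far as it goes: the article does not say which clinics are counted, and it would be wrong to assert that the trial fails its own minimum. It does not remove the problem, because a minimum met by both types together does not size two separate primary analyses.

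Four stronger inferences are tempting, and the documents do not support them:

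- *The pediatric analysis is underpowered.* This is possible but not shown; the third scenario in the table loses almost nothing.
- *Only 21 pediatric clinics remain, because one hosts the alpha test (Section 3.1.2).* Nothing says that this clinic leaves the trial, and the eligibility statement includes all clinics.
- *The type I error is inflated by two primary tests.* That requires a rule that success in either practice type confirms the hypothesis, and none is stated.
- *The separate analyses should give way to one pooled effect.* Children have their own trigger (Section 2.2), and the Discussion expects informatics tools to differ by clinician type. Separate estimates are a defensible choice.

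**Conclusion.** The point holds as a mismatch between the stated sample size and the stated primary analysis. The shortfall of 22 pediatric clinics against 40 is plain arithmetic from the article's own figures and needs no outside assumption. Whichever clinics the minimum counts, the stated size does not support the pediatric analysis.

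The consequence for power is not established. The figures of about 55% to 67% depend on assumed power of 80% to 90% at exactly 40 clinics and on information scaling with clinic number. They illustrate what could be lost and do not estimate this trial's power. The point still matters because it concerns the primary outcome and how a null pediatric result will be interpreted.

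**What to change.** In the analysis section of Specific Aim 2:

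1. State which clinics the minimum of 10 per region counts, and which analysis it sizes.
2. Recompute and state the power, or the detectable effect, of the pediatric analysis with the 22 clinics available.
3. If that falls short, label the pediatric analysis as not separately powered and report it as an estimate with a confidence interval.
4. Keep the separate analyses. Test the adult-pediatric difference with an intervention-by-practice-type term in a joint model that has practice-type-specific period effects. The current text neither specifies nor rules out such a test.

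The cost is some rewording, a re-run of the power calculation and one extra model. No further clinics are needed. The drawback for the sponsor is that the stated pediatric power may look less favorable.

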## 5. Specific Aim 3 (R33): Measure Implementation Success of an Organized FH Diagnostic Evaluation Program

Based on the CMIR [34,35] (Figure 1), this aim will examine implementation outcomes including acceptability, cost, feasibility, fidelity, and sustainability of an FH diagnostic evaluation program (Table 2). The following research questions will be explored:What is the acceptability of an FH diagnostic evaluation program across different demographic regions of the health system?How does the implementation strategy package fit (from Aim 2) within and between different clinic settings and patient populations and what adaptations were made?What are the costs to the healthcare system to implement and maintain an FH diagnostic evaluation program?

### 5.1. Data Collection and Analysis for Each Implementation Outcome

#### 5.1.1. Acceptability

Semi-structured interviews will be conducted with clinicians and patient participants for each of the four steps. Themes assessed in the interviews include empowerment of clinicians to screen and initiate management for FH, acceptability of the FH diagnostic evaluation program, knowledge, attitudes, and beliefs about FH, comfort with the FH diagnostic evaluation, acceptability of strategies for notification of potential FH patients and FH education, and adaptations that occurred. Sessions will be audio-recorded and transcribed verbatim. A thematic analysis approach will be utilized [36].

#### 5.1.2. Cost

Decision analysis and a simulation modeling approach will be applied and the costs of each step of implementation will be estimated utilizing a micro-costing approach, wherein, each component or resource use is estimated, and a unit cost is derived [37]. All models will be developed transparently using recognized methodological and reporting standards to support generalizability and rigor [38]. Decision analysis model development, simulation, and sensitivity analysis will be conducted using decision analysis software (e.g., TreeAge Pro, Palisade Decision Tools Suite) and/or Excel.

